## Abstract

**Background:**

A substantial knowledge base exists on how nurse leaders can support clinical staff in implementing evidence-based knowledge into practice. However, fewer studies are available on how leaders themselves learn and use evidence in their daily work. This study aims to evaluate the effectiveness of an online training course designed to improve the skills of unit leaders by enhancing individual outcomes through evidence-based practice (EBP), team-based outcomes through EBP implementation, and organisational outcomes through the quality of care.

**Methods:**

The effectiveness of the online training course will be evaluated using a cluster randomised two-arm controlled trial. Participants will be unit leaders recruited from hospitals in the Helsinki and Uusimaa Hospital District in Finland. At least 12 units will be represented, with approximately 25 participants in each unit (6 units in each arm). The sample for analysis will consist of at least 300 staff members. In the intervention arm, participants will be invited to join the online leadership course, while participants in the control group will continue practice as usual. The primary outcome is evidence-based practice, while the secondary outcomes are self-esteem, self-efficacy, implementation of EBP, quality of care, as well as work absence and intention to leave. The effectiveness of the intervention on the primary and secondary outcomes will be assessed based on the intention-to-treat principle. Feasibility data will be analysed separately. Sample size calculations are based on preliminary power analyses.

**Discussion:**

To the best of our knowledge, this is the first study to evaluate the effectiveness of an online course on evidence-based knowledge using a full cluster randomised study. By applying evidence-based practices, unit leaders can ensure that clinical decisions are grounded in the latest study results, which will lead to more effective decision-making.

Trial registration

ClinicalTrials.gov, NCT06886581. Registered on 14 March 2025, https://clinicaltrials.gov/study/NCT06886581

**Supplementary Information:**

The online version contains supplementary material available at 10.1186/s13063-025-09207-9.

## Background

The adoption, implementation, and sustainment of evidenced-based practices (EBPs) are increasingly important for health and allied healthcare organisations globally [1]. In Finland, the effectiveness and quality of healthcare and patient safety are key goals of the Ministry of Social Affairs and Health [2]. Managerial-level healthcare workers play an important role in supporting the implementation of evidence-based knowledge into clinical practice [3] by influencing the knowledge, behaviours, decisions, and communication among staff [4]. At the same time, as leaders, managers may hinder the implementation of EBP if their own knowledge or previous experience of working with EBP principles is limited or if they hold negative attitudes towards EBP [5].

There is a growing trend toward organising online leadership training; however, assessments of their effectiveness and cost-effectiveness remain in their infancy, primarily employing quasi-experimental study designs. For instance, Clark et al. [6] evaluated the acceptability and preliminary outcomes of a scalable online learning program aimed at enhancing the leadership competencies of midwives (Leadership Link). While participant satisfaction was reported to be high, only 42% (*N* = 186) completed the full curriculum, and only 76 (40.9%) provided both pre- and immediate post-program survey data. Similarly, Ortega et al. [7] assessed learner performance in an online leadership course involving 289 individuals from 41 countries. Despite receiving more enrolment applications than any other course on the virtual campus, only two-thirds (63.5%) completed the course, and 48.7% rated it. Non-completers cited being too busy with other obligations, encountering technical issues, or finding the course content irrelevant or excessively lengthy. Furthermore, Luo et al. [8] investigated the impact of assigned leadership and its key characteristics on promoting team learning in an online context using a quasi-experimental design with 94 university students. The study found no significant behavioural increase among assigned leaders in reading and reflection tasks, suggesting a moderating effect of learning tasks on leadership impact.

Although there is a substantial knowledge base on how leaders can support staff in implementing evidence-based knowledge into clinical practice, there are far fewer effectiveness studies on how leaders themselves learn and use evidence in their daily work [9]. Therefore, more studies with rigorous research designs are needed to capture the complexity of interventions in improving leadership abilities [10].

This cluster randomisation study will evaluate the effectiveness of an online training course, designed to target unit leaders. The intervention will be delivered at the cluster level, i.e. professionals within clusters (education of unit leaders) [11]. The cluster randomisation study design fits our intention to enhance the application of evidence within entire unit teams, including unit leaders and staff members [12]. Using cluster randomisation will help prevent contamination, which could occur if study participants within the same unit were to be randomised to different groups [13].

### Objectives and hypotheses

The overall aim of the study is to evaluate the effectiveness of an online training course, designed to target unit leaders, to improve EBP skills and implementation as well as the quality of care.

The objectives are as follows:

#### Primary objective

1. To evaluate the effectiveness of the online training course on staff’s evidence-based practice.

#### Secondary objectives

2. To evaluate the effectiveness of the online training course on staff’s self-esteem and self-efficacy.

3. To evaluate the effectiveness of the online training course on leadership for EBP implementation at the organisational level.

4. To evaluate the effectiveness of the online training course on the quality of patient care.

5. To evaluate the effectiveness of the online training course in reducing staff’s absence (sick leave, intention to leave the unit or hospital).

##### ***Hypotheses***

Primary hypothesis:

1. In units where leaders attend the evidence-based online course, staff will have higher scores in evidence-based practice after the course than in the units where leaders do not attend the course.

Secondary hypotheses:

2. In units where leaders attend the evidence-based online course, staff will have higher self-esteem and self-efficacy after the course than in the units where leaders do not attend the course.

3. In units where leaders attend the evidence-based online course, staff will have better EBP implementation scores after the course than in the units where leaders do not attend the course.

4. In units where leaders attend the evidence-based online course, the quality of patient care will be higher after the course than in the units where leaders do not attend the course.

5. In units where leaders attend the evidence-based online course, staff’s work absence and intention to leave the unit or profession will be lower than in those units where leaders do not attend the course.

#### Process evaluation objectives

Feasibility and fidelity of the intervention will be assessed as well as the number of times participants log onto the learning platform, the overall number of completed course tasks, the number of tasks completed by each participant, and the drop-out rate by the number of participants who leave the study early (dropped-out from intervention, no follow-up data). Despite the importance of assessing acceptability and adherence when evaluating an assigned intervention, these qualities are rarely measured and reported in cluster trial publications [13].

## Methods

### Trial design

This study will follow a pragmatic, parallel group (1:1), two-arm cluster randomised, superiority trial design, which aims to compare the effectiveness of an online training course, targeting unit leaders, to improve EBP skills and implementation among staff as well as the quality of care (2025–2028). The Consolidated Standards of Reporting Trials (CONSORT 2010) statement extension to cluster randomised trials was used in designing the study [14]. The SPIRIT checklist [15] guided the study methodology (Additional File 1), and the GREET guideline was consulted when planning this educational EBP intervention [16]. To support the open approach of the trial, the study has been registered at ClinicalTrials.gov (NCT06886581).

To ensure the feasibility of the study design, the study protocol has already been tested in other studies in two countries, Finland and China [17, 18]. The data from these feasibility studies will not be used in this new study.

### Setting

In Finland, the responsibility for organising healthcare services lies with the 21 wellbeing services counties. These counties coordinate the delivery of health and social care services to ensure comprehensive and equitable access for residents within their respective regions [19]. This cluster trial will be conducted in the region of Uusimaa. In 2022, the health and social services sector experienced a higher rate of job growth than other sectors, making it the largest employing industry in Finland [20]. According to national health care statistics in 2023, Finland employed 5138 unit leaders and 77,105 nurses (including registered nurses, midwives, public health nurses, and paramedics with a bachelor’s degree) [21].

#### Eligibility of the clusters and individual participants

For a cluster to be eligible for participation, it should comprise a unit providing specialised or primary care with at least 20 staff members (unit leaders and other staff) and be interested in joining the study. A ‘unit’ here refers to a ward, department, or any independent operational entity that has its own immediate leader or supervisor. Units will be excluded if they have low staff capacity (fewer than 20 total staff members), if they do not provide treatment to patients (e.g., supply management, laboratory), or if they are expected to undergo significant operational changes or closures.

The online training course is designed to target unit leaders working in the social or health care sector in a managerial position. Unit leaders were selected as the primary target group of the course because they represent important first-level actors in the implementation process of evidence-based knowledge into clinical practice [22]. To be eligible for participation, unit leaders should 1) have a professional licence to work in the health or social care sector, 2) have an official managerial position at the study organisation, 3) demonstrate a willingness to join the study, 4) represent any gender, 5) be able to speak, read, and write in Finnish, 6) and give (individual level) informed consent to join the study. Unit leaders with a background in nursing or medicine (doctor, dentist) should hold positions in strategic, middle, and supervisory management within social and healthcare units [23]. Unit leaders on long-term sick leave or study leave will be excluded.

In Finland, there are no legal regulations for management and supervisory positions; these are defined by the employer [24]. However, in social and health care positions, the minimum requirement is a bachelor’s degree in health care from a university of applied sciences (e.g., registered nurse, physiotherapist, radiographer) and being licensed by the National Supervisory Authority for Welfare and Health [25]. Medical and dental specialists receive training to manage demanding diagnostic methods and to perform in roles of healthcare leadership, administration, planning, interdisciplinary collaboration, guidance of learning, and assessment of competence within their work community [26]. For nurses in Finland, the Union for Health and Social Care Professionals recommends an advanced university degree or a relevant advanced degree from a university of applied sciences for strategic and middle management positions (e.g., administrative chief nurse, chief nurse, or nursing director) [24]. The closer the leader’s role is to patient care, the more critical their nursing expertise and the application of evidence-based practices are [23].

Any staff members (e.g., registered nurses, assistant nurses, or any professional staff members with social and health care degrees) working in the same units as the unit leaders who are willing to join the study will be eligible for participation. Staff members who are off duty (family leave, long-term sick leave, study leave, or any other reason) will be excluded from the study.

To secure the privacy of the unit leaders of the organisations, the Chief Executive Officers in Nursing will act as a contact person for each study organisation. The contact person will screen potential units to determine whether their leaders fit into the following eligibility criteria.

### Interventions

The units will be randomised into two groups: an evidence-based leadership training (experimental) group and a passive control group.

For the evidence-based leadership training (experimental) group, the intervention will be targeted at the cluster level (i.e. tasks included in the intervention will be done in close collaboration with members of the same unit). The participants in the experimental group will join a seven-month online training course aiming to improve evidence-based leadership practice. The structure of the course will follow the steps of the evidence-based approach: [1] each participant will identify their specific unit problem to be solved together with the team and the unit leader will address this problem during the course; [2] organisational data will be collated and analysed to understand the key problem of the unit; [3] scientific literature will be searched for and critically appraised; [4] the views of stakeholders (patients, family members, etc.) will be considered along with implications; and [5] all sources of information will be collated together by the unit leader together with the team, after which the solution will be implemented into practice [17]; the actual situation will be evaluated [27]. Each module includes specific learning material (slideshow presentations, scientific articles), peer-group discussions, clinical exercises, and self-assessment and self-reflection [17]. All course tasks will be arranged so that leaders will work together with their team.

The online training intervention will be run in small groups with unit leaders (about 15 participants in each training group). Tutors (1/group) with an academic and/or healthcare professional background will follow participants’ and their team’s learning process in each small group. Tutors will receive centralised training on the study requirements through a total of 4 h of hands-on training sessions. These sessions will cover topics related to the tutor’s role, which includes carefully monitoring participants’ engagement (returned tasks and course drop-outs, peer discussions, and any other activity), answering practical questions related to the course via group chat and/or email, and giving feedback on all course assignments. Although no makeup sessions will be organised if a participant misses a training session, individual participants (or the tutor) may still request extended time to complete their tasks. However, a unit leader can choose to stop participating in the online course at any time, for any reason, without staff needing to withdraw from the entire study (i.e. the staff can still provide follow-up data). A student may be removed from the online course if, for example, they behave unethically towards other students. At the beginning of the course, the ethical guidelines regarding online education will be presented.

In line with the Finnish National Board on Research Integrity (TENK) guidelines [28], no compensation or reimbursement will be paid to the study participants. No additional support, training, or mentoring related to leadership skills will be offered by the research team after the intervention period.

Details of the assumptions and intervention mechanism, pedagogical approaches, learning process, structure, and content of the course are described in the intervention protocol [17]. In addition, the structure and content of the intervention are described in Additional File 2 using the GREET checklist [16].

No specific activities will be organised for the passive control group participants.

### Outcomes

The data will be formed based on the characteristics of each unit and its participants, outcome data, course feedback, and feasibility data of the online training course.

#### Characteristics of the units and participants

Each unit’s clinical specialty, number of beds, and total number of staff will be collected based on unit records, with the help of the unit leaders and a contact person for each organisation. The researchers will not have access to organisational databases. The age, gender, degrees, position and length of working experience of each participant will be collected as part of baseline data.

#### Outcomes

The outcomes are targeted to evaluate the effectiveness of the evidence-based online course on an individual, team, and organisational level [4]. The primary endpoint with respect to the effectiveness of the training course is improvement in evidence-based practice (EBP) from baseline to follow-up (month 7), measured immediately after the intervention using an electronic survey administered to the unit leaders and staff.

Primary outcome.

*Evidence-based practice*: The Evidence-based Practice Questionnaire (EBPQ) [29] assesses the implementation of evidence-based practice (24 items, score 1–7, three sub-scales), focusing on [1] knowledge/skills (14 items, score 1–7, 1 = Poor–7 = Best, range 14–98, a higher score represents greater knowledge in EBP); [2] attitudes (4 items, score 1–7, range 4–28; a higher score represents a more positive attitude toward EBP); [3] evidence-based practice (6 items, score 1–7, 1 = never, 7 = frequently, range 6–42, a higher score represents more use of EBP). The instrument’s internal consistency has been rated as good, as indicated by a Cronbach’s alpha of 0.87 across the full scale [29].

Secondary outcomes.

The data for the secondary outcomes will be collected at baseline and at month 7.

*Self-esteem*: The Rosenberg Self-Esteem Scale (RSE) [30] evaluates individual self-esteem with a 10-item unidimensional scale by focusing on both positive and negative feelings about the self (4-point Likert scale, 1 = strongly agree–4 = strongly disagree). The sum score ranges 10–40, and a higher score indicates higher self-esteem. The RSE has shown high internal consistency reliability, with an average Cronbach’s alpha of 0.90 [31].

*Self-efficacy*: The General Self-Efficacy Scale (GSE) [32] assesses optimistic self-beliefs in coping with a variety of difficult life demands using 10 items (4-point Likert scale, 1 = not at all true–4 = exactly true). The sum score ranges 10–40, and a higher score indicates better coping abilities. The GSE scale has shown good reliability and unidimensionality across 25 countries, with an overall Cronbach’s alpha of 0.86 [33].

*The implementation of EBP*: The Implementation Leadership Scale (ILS) is available in two versions, one for staff and one for supervisors [22]. The scale comprises a 12-item questionnaire measuring leadership in EBP implementation. It consists of four subscales: 1) proactive leadership, 2) knowledgeable leadership, 3) supportive leadership, and 4) perseverant leadership. It is scored from 0 (not at all) to 4 (to a very great extent), with a higher score representing stronger implementation of EBP. The ILS has demonstrated strong psychometric properties, including face, content, and construct validity as well as internal consistency and convergent validity across multiple health professional groups [34]. Internal consistency reliability has been found to be high, with a Cronbach’s alpha of 0.98 for the total scale and 0.95–0.96 for the subscales [22].

*The quality of care*: Patient death, the number of reported complaints, and medication errors will be collected from hospital records after the training course (to be balanced according to follow-up time).

*Work absence and intention to leave*: The number of days staff are absent during the course (e.g., sick leave) and intention to leave will be measured: [1] “In the last six months, how often have you planned to leave your unit”; [2] “In the last six months, how often have you planned to leave your hospital”; and [3] “In the last six months, how often have you planned to leave your profession” using a five-point scale (0 = never; 1 = now and then; 2 = quite often; 3 = very often; 4 = all the time).

After the course (month 7), course feedback will be collected (8 items developed for the study): [1] “This course was appealing to me”; [2] “I felt happy when I participated in the course”; [3] “Participation in the course required too much effort from me”; [4] “It was worth participating in this course”; [5] “I found this course valuable”; [6] “I was able to meet the requirements of the course”; [7] “This course fits well with my personal values”; and [8] “I would recommend the course to others”. Participants will consider the propositions with five possible answers (1 = completely disagree; 2 = disagree; 3 = neither agree nor disagree; 4 = agree; 5 = completely agree). Possible contamination of the study groups and any perceived adverse event or harm will be screened for during and after the intervention (months 0–7) (yes, no, not sure).

Further, feasibility and fidelity of the intervention will be assessed after course completion (month 7): [1] the number of total logins to each module (*n*); [2] the number of participants who logged in to each module (*n*, %); [3] adherence to the course, measured by the number of returned course tasks out of all possible tasks (*f*, %); [4] adherence to the course tasks, measured by the number of participants who returned course tasks for each module (*n*, %); [5] drop-out from the intervention, measured by the number of participants who leave the intervention early; [6] drop-out from the study, measured by the number of participants who leave the study early.

None of the content of the participants’ learning material, self-reflections, or peer discussion data on the Moodle platform will be analysed in this study.

Important protocol modifications will be communicated to the relevant parties, including the Ethical Review Board and the study organisations. Any modifications will be reported in the trial registry (ClinicalTrials.gov) and in the final report.

Outcomes, instruments, and specific timelines for each outcome assessment are described in Fig. 1.

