### Recruitment

To minimise risks of recruitment bias, recruitment of the participants will be done before randomising clusters [11]. An invitation to participate in the study will be sent to the supervisors of all units initially interested in joining the research. The email will include a link to study information and electronic informed consent with the Research Electronic Data Capture tool (REDCap) [40]. After a participant gives electronic informed consent, REDCap will lead them to a baseline survey (background information of the participants of the specific units, baseline data). After baseline data collection, unit leaders will be allocated to the study group as their unit.

All staff members who are working in the same unit as the participating unit leaders will be invited to join the study. First, staff members will receive a general invitation email, including a link to a site for baseline data collection, sent by the unit leader (for privacy reasons) to explain the purpose of the study and its practical arrangements. If the staff member is willing to join the study, they will give electronic consent (REDCap) and respond to the electronic surveys; but they do not join online training. Again, after providing baseline data, each staff member will be allocated to the same study group as their unit leader. The invitation email will include an explicit statement that participation is entirely voluntary, that non-participation will not have any consequences for staff, and that all responses will remain confidential. Participants will also be informed about the study’s purpose, procedures, and any potential risks or benefits. It is emphasised that staff members are not compelled to participate against their will or under pressure. Since the link to the data collection site that will be sent by the unit leader is general (non-specified with staff member’s name), the unit leaders will not be aware of who is joining the study or who is not. In addition, the study invitation will be framed as an opportunity for professional development or improvement rather than a requirement, making it less likely to be perceived as coercive.

To enhance recruitment and reach the target sample size, reminders will be sent via email to potential participants. If necessary, recruitment will be expanded to new locations and departments.

An overview of the trial profile is described in Fig. 2.

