Sensitivity analyses will be conducted for units in which participation in online training is low to evaluate whether intervention fidelity has any effect on the results of the primary outcome. Results will be expressed using rate ratios, odds ratios, or least-squares mean differences with corresponding 95% CIs, depending on the type of outcome.

As our study will be a cluster randomised controlled trial, its analysis requires special consideration of the correlations within and between the clusters. First, in the sample size calculation, a clustering effect was assumed and accounted for as the ICC coefficient. Second, for the primary analysis, the intracluster (intraclass) correlation coefficient (ICC) will be reported as the proportion of the total variance of the outcome that can be explained by the variation between clusters [14]. For data analysis, the mixed effects model or two-level multilevel models that consider clustering effects will be used. In the model analysis, the variation in the outcomes among clusters will be estimated and tested for significance. Third, the overall efficacy of the outcomes will be estimated after considering the clustering effects.

In addition, covariate analysis will be conducted to control for potential confounding factors in statistical modelling. Participants’ age (novice, senior) and gender (male, female, other), status (unit leader, other staff member) and the engagement of course tasks (number of returned tasks by each participant in the intervention group) will be included in the analysis.

Statistical analyses will be performed with the SAS System for Windows, version 9.4 (SAS Institute Inc) and SPSS, versions 25.0 to 27.0 (IBM Corp). Because no adjustments for multiplicity of testing will be made, only 95% CIs will be reported for the secondary outcomes.

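### The primary question is about staff, but the primary endpoint and model appear to include the unit leaders who take the course, so the arm effect mixes a direct effect on trainees with the staff effect

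*Protocol article*

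**What the plan says.** The primary objective is "To evaluate the effectiveness of the online training course on staff’s evidence-based practice". The primary hypothesis is that, where leaders attend, "staff will have higher scores in evidence-based practice after the course than in the units where leaders do not attend the course". The abstract describes the analysis sample as at least 300 staff members.

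The Outcomes section defines the primary endpoint as improvement in EBPQ from baseline to month 7, "measured immediately after the intervention using an electronic survey administered to the unit leaders and staff". Data management and statistical analysis puts this change into a linear mixed model with respondents nested in units. Among the covariates it lists "status (unit leader, other staff member").

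On exposure, the Interventions section says: "The online training intervention will be run in small groups with unit leaders (about 15 participants in each training group"). Recruitment says that staff answer the surveys "but they do not join online training". Interventions adds: "All course tasks will be arranged so that leaders will work together with their team".

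The word staff is not used in one sense. The unit-size criterion under Eligibility counts unit leaders among the staff members. The later eligibility text for staff, and Recruitment, treat staff as the people who work alongside the leaders.

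For the implementation outcome, Outcomes says: "The Implementation Leadership Scale (ILS) is available in two versions, one for staff and one for supervisors". Hypothesis 3 is about staff scores. The protocol does not say which version supplies the analysed score.

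**The concern.** Leaders and staff receive different things. Leaders receive the course itself. Staff receive whatever passes to them through joint tasks and changed leadership, and the primary hypothesis asks whether that second route works. If both groups enter one model with one arm effect, a gain confined to the leaders moves the result that will be reported as the effect on staff.

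The status covariate does not cure this. As a main effect it removes the average leader-staff difference in change, taken over both arms. The arm coefficient is still forced to be common to both groups, so it is their weighted average. At stake are the size of the reported staff effect and, if staff do not benefit at all, the type I error of the primary test.

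**Working it through.** **Inputs from the Sample size section.** Difference 10, SD 20, ICC 0.03, 25 per unit, 6 units per arm, 80% power, two-sided 5%.

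**Assumptions, not in the protocol.** 1 to 3 leaders among 25 analysed per unit; a leader effect D of 20 or 30 EBPQ points. The engagement covariate is set aside here.

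**1. The plan's own figure.**
- Individually randomised: 63 per arm.
- Design effect: 1 + 24 × 0.03 = 1.72, so 63 × 1.72 = 108.4 per arm, or 4.3 units.
- With a t test on 2(k − 1) cluster degrees of freedom, power is 75.2% at k = 5 units per arm and 84.4% at k = 6.
- Six per arm is the smallest number reaching 80%, so 12 units and 300 participants are reproduced.
- Standard error at k = 6: 20 × √(2 × 1.72 / 150) = 3.03.

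**2. What the pooled arm coefficient estimates.** With leader share f equal in both arms:

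pooled effect = (1 − f) × staff effect + f × leader effect

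The bias for the staff effect is therefore f × (leader effect − staff effect).

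**3. True staff effect 0.** Rejection rates use SE 3.03 and t on 10 df.

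| Leaders in 25 | f | D | Pooled effect | Rejection rate (nominal 5%) |
|---|---|---|---|---|
| 1 | 0.04 | 20 | 0.8 | 5.7% |
| 1 | 0.04 | 30 | 1.2 | 6.5% |
| 3 | 0.12 | 20 | 2.4 | 11.1% |
| 3 | 0.12 | 30 | 3.6 | 19.0% |

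**4. True staff effect 5, D = 20.**
- 1 leader: 0.96 × 5 + 0.04 × 20 = 5.6.
- 3 leaders: 0.88 × 5 + 0.12 × 20 = 6.8.

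**5. Could leaders alone produce the planned 10 points?** That needs D = 10 / f: 250 points at 1 leader and 83 at 3. The EBPQ total runs from 24 to 168, a span of 144.

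**6. Is the range of f reasonable?** The plan approaches 1,238 people, about 103 per unit over 12 units. With staff response and completion of 42% × 58%, and every leader responding, f is 3.9% for 1 leader and 10.9% for 3. This agrees with the 4% to 12% used above.

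**7. Power of a staff-only analysis.** Six units per arm, same difference, SD and ICC, t on 10 df.

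| Staff per unit | Power |
|---|---|
| 24 | 83.6% |
| 23 | 82.7% |
| 22 | 81.7% |
| 20 | 79.5% |

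**The case against.** The best counter-argument is that pooling is inferred and may be intended. The analysis section glosses respondents as staff members and the abstract counts staff, so the primary model might already be staff-only. In the other direction, the unit-size criterion counts leaders as staff, and the Background states the aim of raising evidence use in whole unit teams including leaders, so a whole-unit effect would suit a cluster-level intervention. Both readings have support, and neither removes the problem. Under the first, the status covariate has no variation. Under the second, the hypothesis should not be worded as a contrast between staff and the leaders who attend. The protocol has to choose one.

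It is also fair that staff are not unexposed: they work on the course tasks. That narrows the likely gap between the two effects but does not make them equal. The protocol describes a unit as having its own immediate leader, in the singular, which favours the 4% case and a small bias. The training-group size of about 15 does not establish several leaders per unit, because nothing says that one group is filled from six units.

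Two stronger readings are tempting and not supported. A reader might infer that the trial could not tell whether the course reached staff. Position is collected at baseline and status is recorded for analysis, so a staff-specific estimate can be computed; it would just not be the pre-specified primary result. A reader might also infer that leaders' self-ratings on the ILS are pooled with staff ratings. The protocol says only that two versions exist. It does not say that leaders rate themselves or that the versions are combined.

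**Conclusion.** The point stands as an inconsistency between the primary question and the primary analysis, with a modest expected effect. As written, the objective and hypothesis concern staff, while the endpoint and covariate list indicate a model that includes the leaders, and a main effect for status leaves the leaders' own treatment effect in the arm coefficient.

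The direction is not certain. The staff effect is overstated only if leaders gain more than staff, which is plausible for the people who take the course but is assumed. On a 20-point leader effect and no staff effect, the overstatement is 0.8 to 2.4 points against a planned difference of 10, with type I error of about 5.7% to 11% for 1 to 3 leaders in 25. Leakage alone is very unlikely to produce the planned 10 points. The reason to act is that the primary result should answer the stated question and the correction costs almost nothing.

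**What to change.** Define the primary analysis population as participating staff other than unit leaders, in both arms. Drop status from that model, where it no longer varies, and count only non-leader staff toward the 300. Report the leaders, or the pooled whole-unit effect, as a pre-specified secondary analysis. Use staff in one sense throughout, including the unit-size criterion. For hypothesis 3, state that the staff version of the ILS supplies the analysed score.

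If the whole-unit effect is what the trial wants as primary, the objective and hypothesis should say so, and the staff-specific effect should be pre-specified beside it.

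The cost is wording, settled before outcome data are compared by arm. No new data are needed, since position is already collected. If the removed leaders are not replaced, power falls from 84.4% to between 81.7% and 83.6% with 22 to 24 staff per unit. Replacing them takes 12 to 36 more analysed staff (1 to 3 in each of 12 units) and restores the planned power.
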